### Interventions

The internet- and tele-based interventions are described according to the *Template for intervention description and replication* (TIDieR) [51], see Supplementary material. They are briefly outlined below.

#### Tailored IMIs

Seven IMIs are provided by the GET.ON Institute (www.geton-institut.de). Their effectiveness in the prevention and treatment of mental disorders has been demonstrated in more than 30 randomised controlled trials [19, 20, 52–65]. The IMIs are individually tailored to the participants based on their symptoms, risk profile and needs, and follow the selective prevention approach (e.g. providing trainings for a group with increased risk for mental disorders). The different IMIs are addressing risk factors for the incidence of depression including subclinical depressive symptoms [66], insomnia [67], stress [68], anxiety [69], chronic pain [70], harmful alcohol use [71, 72] and subclinical depressive symptoms in the context of diabetes [73]. The IMIs are adapted to the target group of farmers, foresters and gardeners in terms of content (e.g. descriptions of mock individuals facing similar struggles) and graphics to meet the needs of the participants. Variation of content and duration of the seven IMIs is illustrated in Fig. 2.

**Fig. 2 Fig2:**
[figure not shown]
Online content, guidance and duration of the GET.ON online health trainings

To begin the intervention phase, the participant completes a computer-adaptive psycho-diagnostic assessment which is based on self-report questionnaires assessing mental health issues. The type of online training is chosen during the initial interview with the e-coach depending on the participant’s symptom profile, needs and preferences. The modules include psychoeducation, testimonials of mock individuals, in-depth exercises, a diary and homework to improve mental health and wellbeing. Depending on the training type, participants have access to additional modules. After each module, the participant receives individual feedback by email or by phone from the e-coach which helps to improve adherence of e-health interventions [74].

The e-coaches are psychologists with a university degree who have at least started a psychotherapeutic training. The training of the e-coaches consists of supervision by licensed psychotherapists in CBT training and information about IT-matters. A detailed description is published in the study protocols elsewhere [40, 75–80].

#### Personalised tele-based coaching

The personalised tele-based coaching is provided by the company IVPNetworks (www.ivpnetworks.de) and focuses on general mental health problems. The coaches are psychologists with trainings either in cognitive behavioural therapy, systemic therapy, psychodynamic psychology, hypnotherapy or other therapeutic trainings. Licensed psychotherapists are responsible for supervision. The coaches support participants in recognising and understanding conflict patterns in order to effectively cope with issues by activating their own resources. This is pursued by approaching the participant’s personal situation and stressors (e.g., financial burden, family problems, work-related stress).

Participants are registered with their contact information in the IVPNetworks management and documentation platform (IVPnet 2.0). A case manager at IVPNetworks assigns the participant to a coach. The coaching is personalised in terms of amount, frequency and duration of the sessions, depending on the individual participant’s needs. Personalised coaching means that there are no standardised manuals or fixed procedures for the coaching. Different therapeutic methods are used depending on the therapeutic background of the coach (which will be monitored in the study). If indicated, participants are supported in finding on-site social and health care services to complement the tele-based coaching (e.g., socioeconomic consultants, agricultural family counselling). Alternatively, on-site coaching can be arranged if a participant no longer prefers tele-based coaching. Common content and duration of the personalised tele-based coaching at IVPNetworks are illustrated in Fig. 3.

**Fig. 3 Fig3:**
[figure not shown]
Content and duration of the personalised tele-based coaching at IVPNetworks

In addition to the personalised tele-based coaching, IVPNetworks offers a crisis hotline that can be used 24/7 by those insured at SVLFG. The crisis hotline is managed by trained psychologists and is a resource for acute psychological emergencies and crisis situations. As part of the crisis hotline, up to five follow-up contacts are possible.

### Participants

The study design includes two groups of participants involved in the implementation process:

#### Group 1: insured persons at SVLFG

Inclusion criteria for insured persons at SVLFG includes: being an insured member of the health insurance scheme OR the pension fund of the SVLFG, being an agricultural contractor OR a collaborating spouse OR a family member or a pensioner, being over 18 years old, having access to the internet and/or a telephone, and providing informed consent.

Persons will be excluded if they currently suffer from a mental disorder and need extensive therapeutic service. Individuals may be excluded during the consultation in the call centre (if the interested insured person reports a mental disorder), during the assessment by the service provider or during their participation in case of a suspected mental disorder. If there is a suspicion, the external service provider advises the participant that a consultation with a general practitioner is recommended. The insured individual gets support in the search for further treatment options. In addition, people can be excluded for the tele-based intervention, if they have substantial hearing impairment or for the online interventions, if they have a visual impairment.

There are 465,000 eligible insured members of SVLFG nationwide, and the sample size is not capped. The number of participants enrolled in this study depends on the rollout stage of the implementation. Eligible insured persons can choose the specific intervention based on their preference and needs which reflects the conditions of routine care. A sample size of *N* = 100 per intervention is desirable to achieve reliable results. Based on previous experiences in the pilot phase of the implementation in two federal states, we expect a sample size of approximately 500 to 800 participants for the national implementation area.

#### Group 2: staff-participants at SVLFG, GET.ON and IVPNetworks

##### Field worker, in-house staff and call centre agents at the implementing company SVLFG

Approximately 350 field workers visit the insured members on-site. In-house staff counsel the insured persons by telephone. Both field workers and staff advise insured members on technical prevention, rehabilitation, etc. and additionally inform and advise members regarding the internet- and tele-based prevention services. They also forward interested persons to a nationwide call centre. Depending on the rollout phase (which includes a training on all health services offered by the SVLFG), the field workers begin advising members on the internet- and tele-based interventions at different times. Twenty-five call centre agents advise the insured individuals on various health offers including the newly implemented internet- and tele-based interventions. Additionally, call centre agents check the insurance eligibility criteria and are responsible for the enrolment in the prevention services.

Thus, implementation of internet- and tele-based interventions requires that these employees undergo changes to their work environment, especially at the behavioural level, by adapting their previous working routines to the new requirements.

##### Implementation team of SVLFG

Members of the implementation team are responsible for the planning and realisation of the implementation activities. Employees who work in two or more roles (e.g. as a field worker, in-house staff and/or call centre agent) are excluded from the staff surveys for field workers, in-house staff and call centre agents to avoid conflation of the data, as such persons cannot perform both roles simultaneously without bias.

##### Coaches at GET.ON and IVPNetworks

Coaches are involved in the delivery of the internet- or tele-based interventions and work as psychologists or therapists on a freelance basis or employment contract for GET.ON or IVPNetworks.

Approximately 150 staff-participants at GET.ON, IVPNetworks and SVLFG are expected to participate in the study. All employees of the described staff-groups who sign the informed consent are able to participate in the study. There are no specific eligibility criteria. If additional professional groups become involved in the future course of the implementation of these services, it will be decided whether these employees will be included in the surveys.

### Measurements

The used measures are summarised in Table 1, followed by a description of each RE-AIM dimension and selected outcomes. Measurements include routine data, staff reviews of intervention consultations as well as usage of the interventions by insured individuals, online-assessments, qualitative interviews and focus groups.

**Table 1 Tab1:** RE-AIM dimensions, measures and assessments

Dimension	Measure	Source	Assessment type	Time point
**REACH (individual level)**	Number and characteristics of potentially eligible insured individuals	SVLFG	Routine data	18 m
	Exclusion, referral und uptake rates; Completer rating from clinician’s judgement (Helping Alliance Questionnaire)	GET.ON Institute / IVPNetworks / SVLFG; GET.ON and IVP coaches	Reportings; Online-Assessment	Every 3 months; after participant is defined as (non-) completer
	Estimated number of people exposed to the recruitment, recruitment response rate in general as well as specific recruiting strategies	GET.ON Institute / IVPNetworks / SVLFG	Reportings	Every 3 months
	Representativeness of participants compared to eligible insured individuals and interested, but not participating insured persons	SVLFG	Routine data	18 m
**EFFECTIVENESS (individual level)**	Depressive symptoms (Patient Health Questionnaire 9), perceived stress (Perceived Stress Scale 4), generalised anxiety disorder (Generalised Anxiety Disorder 7 scale), somatisation (Somatic Symptom Scale 8), health-related quality of life (Assessment of Quality of Life 4D), subjective capacity to work (Subjective Prognostic Employment Scale)	Insured person	Online-assessment	T0-T2^a^
	Patient satisfaction (Client Satisfaction Questionnaire adapted for internet interventions), side effects (Assessment of Negative Effects of Psychotherapy)	Insured person	Online-assessment	T1^a^
**ADOPTION (organisational level)**	Number, proportion and characteristics of involved employees per organisation, characteristics of federal states and rollout areas, characteristics of insured persons and type of agricultural holding	GET.ON Institute / IVPNetworks / SVLFG	Sociodemographics of employees, routine data	R0^b^ Continuous
**IMPLEMEN-TATION (individual + organisational level)**	*Characteristics of the interventions:*			
	- Adaptations (TIDieR checklist)	GET.ON Institute / IVPNetworks	Reportings	Mid and end of the project
	- Usage of the intervention (e.g. adherence, duration and frequency of contacts)	GET.ON Institute / IVPNetworks	Reportings	Continuous
	- Credibility (Credibility Expectancy Questionnaire) and perceived (dis-)advantages	SVLFG staff- participants	Online-assessment	R0 / R1 / R2 / R3^b^
	- Costs for the intervention	SVLFG	Reportings	Every 3 months
	*Outer Setting:*			
	Acceptance, relevance, utility	Insured person GET.ON Institute / IVPNetworks	Online-assessment Interviews Reportings (e.g. adherence)	T1^a^, T1^a^ Continuous
	*Inner Setting:*			
	- Leadership support (Implementation Leadership Scale)	SVLFG staff-participants	Online-assessment	R0 / R1^b^
	- Organisational willingness to change (Organisational Readiness for Implementing Change questionnaire)	SVLFG staff-participants, implementation team	Online-assessment	R0 / R1 / R2 / R3^b^
	*Characteristics of individuals:*			
	- Degree of normalisation (NoMAD)	SVLFG staff-participants	Online-assessment	R0 / R1 / R2 / R3^b^
	- Determinants of Behavioural Change (Discriminant Content Validation of the TDF Questionnaire)	SVLFG staff-participants)	Online-assessment	R1^b^
	- Barriers and facilitating factors at the consultations	SVLFG staff-participants	Focus groups	11/2017–02/2019
	*Process:*			
	- Evaluation of the implementation process (e.g. implementation activities, barriers and facilitating factors)	Implementation team	Interview	Every 6 months
	- Dissemination activities	SVLFG	Reportings	Every 3 months
	- Usage by employees	SVLFG staff-participants	Reportings	Every 3 months
	- Implementation costs	SVLFG	Reportings	Every 3 months
**MAINTENANCE (individual + organisatonal level)**	Sustainability of interventions (effectiveness)	Insured	Online-Assessment	T2^a^
	Referrals back to SVLFG and use of further offers	GET.ON Institute / IVPNetworks / SVLFG	Reportings	Continous
	Evaluation of the current implementation and further use of the technologies	SVLFG staff-participants	Online-assessment	R3^b^
	Sustainability of implementation (referral and uptake rates)	GET.ON Institute / IVPNetworks / SVLFG	Reportings	R3^b^

Notes

^a^time of insured-assessment depends on the date of intervention start

^b^time of employee-assessment depends on the date of the rollout in the specific area

*Abbreviation*: *m* month

Assessments: T0 (pre intervention), T1 (3 months after starting the internet-based training / 6 months after starting the tele-based intervention), T2 (12 months after starting the intervention)

Rollout: R0 (rollout start), R1 (6 months after rollout), R2 (12 months after rollout), R3 (18 months after rollout)

#### Reach

To assess reach, the number and characteristics of the potentially eligible insured individuals at SVLFG, as well as exclusion, referral and uptake rates of the internet-, tele-based and on-site group preventive services will be reported. The following uptake levels will be considered in order to illustrate different levels of engagement:
Referral rates: The absolute number of: a) referrals by the SVLFG field workers (operationalised as consultations about internet- and tele-based interventions), b) referrals by the call centre agents to the internet- and tele-based prevention services (IMIs: sending out a code for the registration at the online-platform, tele-based coaching: registration on the IVPnet platform), and c) the first contact with the external service provider (IMIs: first log in at online-platform to symptom screening; tele-based coaching: agreement for first tele-based coaching appointment).Uptake rates of internet- and tele-based interventions:
Intervention not started: The absolute number of referred persons who completed the assessment phase (IMIs: psycho-diagnostic assessment, tele-based coaching: first coaching assessment session) after the first contact with the external service provider, but have not started the intervention.In treatment: The absolute number of persons who have started the intervention after assessment phase (IMIs: first login into first module; tele-based coaching: receive tele-based coaching at minimum second session).Treatment not completed: Absolute number of persons who completed less than 50% vs. 70% of the intervention (IMIs: completed less than 50% vs. 70% maximal online modules within 13 weeks, have not logged in for at least 8 weeks or have interrupted the training for other reasons; tele-based coaching: completed less than 50% vs. 70% of the total call minutes, did not answer for at least 8 weeks or cancelled the coaching for other reasons).Treatment completed: a) In previous e-mental health studies, the completer criteria differed between 50 to 100% of completed units [81–84]. Research also indicates that a minimal treatment for subthreshold depression (e.g. six phone calls each with a maximum of 15 min) can also be effective in preventing MD [85]. Therefore, we defined two criteria with different treatment dosis as following: Absolute number of persons who completed at least 50% vs. 70% of online modules or call minutes. b) Clinical judgment by coaches at GET.ON Institute and IVPNetworks assessed with the Helping Alliance Questionnaire (HAQ) based on 11 items [86] in order to supplement the quantitative criteria for completion.Uptake of other services: This may include the crisis hotline, a second guided IMI, diagnostic clarification at IVPNetworks (via telephone or on-site), referrals to social or health service centres (e.g. socioeconomic or family consultants) during the tele-based coaching.

In addition, the estimated number of people exposed to recruitment materials and the associated response rate will be assessed. Specific recruiting strategies are tested to examine successful ways of addressing the target population. To provide representative information, interested but not participating individuals, and enrolled participants will be compared based on routine data. Differences in reach between the internet-, tele-based and on-site preventive services will be investigated as well.

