##### Outer setting

Constructs including participants’ needs and resources are related to the CFIR dimension ‘outer setting’ [43]. In assessing the outer setting, participant satisfaction is measured by using a German Version of the Client Satisfaction Questionnaire adapted for internet interventions (CSQ-I; α = 0.93) based on 8 items [65, 98]. The participants are asked about the usefulness and relevance of the interventions. Acceptance of the interventions is indirectly recorded via non-completer rates (indicator, see above). Approximately 20 semi-structured interviews each with participants from GET.ON chronic pain, from the six remaining IMIs and from the tele-based coaching will supplement the data collection and provide insights into the participants’ experience (e.g. acceptance, satisfaction, barriers and facilitators for intervention usage) with the internet- or tele-based interventions. The interview guide is based on the Unified Theory of Acceptance and Use of Technology (UTAUT) model [99] and the Discrepancy Theory of Satisfaction [100] with regards to the dimensions: technical quality of care, psychosocial quality of care, organisational conditions, spatial and technical equipment, treatment outcome, continuity of care and financing [100].

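### The completed and not-completed categories are not mutually exclusive as written, and the text does not define the tele-coaching denominator

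*Protocol article*

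**What the plan says.** The Reach section of the Protocol article lists the uptake levels.

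- **Not completed, stem:** "Absolute number of persons who completed less than 50% vs. 70% of the intervention".
- **Not completed, IMI bracket:** "completed less than 50% vs. 70% maximal online modules within 13 weeks", then, after a comma, "have not logged in for at least 8 weeks or have interrupted the training for other reasons".
- **Not completed, tele bracket:** "completed less than 50% vs. 70% of the total call minutes, did not answer for at least 8 weeks or cancelled the coaching" for other reasons. No number of weeks limits the dose item.
- **Completed:** "Absolute number of persons who completed at least 50% vs. 70% of online modules or call minutes". No time limit and no activity condition are attached. A coach rating is added "in order to supplement the quantitative criteria for completion".

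On the tele dose, the section Personalised tele-based coaching says: "The coaching is personalised in terms of amount, frequency and duration of the sessions".

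The categories are used in four places:

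- Outer setting: "Acceptance of the interventions is indirectly recorded via non-completer rates".
- Measuring implementation success names both categories among the uptake levels.
- Quantitative analysis uses completers as one of the groups for effectiveness.
- The same section regresses uptake rates on intervention type.

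**The concern.** Two labels that read as opposites should put each starter in exactly one class at a given threshold. Here the two rules have different time limits, and only one of them mentions inactivity. Two analysts working from the same provider reports could code the same person differently, and neither would be departing from the text.

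For tele-coaching, a percentage of a total that the text does not define, for a service whose amount is individual, may reflect the choice of denominator more than the participant's adherence.

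At stake are the acceptance indicator, the completer and non-completer levels within implementation success, the membership of the completer subgroup, and the comparison of uptake between services. Table 1 also times the coach rating from the moment a participant is assigned one status or the other, so an unstable status affects data collection too.

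**Working it through.** The protocol states no completion or inactivity rate, so there is no figure of its own to reproduce. The check sets the rules side by side and then shows how the counts would behave under assumed inputs.

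**1. Test cases against the two rules**

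| Case | Completed? | Not completed? |
|---|---|---|
| IMI, below 50% at week 13, passes 50% in week 14 | Yes, no time limit | Yes at week 13; nothing says the status is revised |
| IMI, 80% of modules, then no login for 8 weeks | Yes, at 50% and 70% | Yes if the bracket items are alternatives; no if the stem limits them all |
| Tele, active, threshold not yet reached | No | Dose item is met from the start, as no window applies |

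The first case arises from the one-sided 13-week limit and does not depend on how the inactivity item is read. The same holds at 70%. One might judge the stem on the final dose and so rescue this person, but then the 13-week limit would not affect the final classification.

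The IMI denominators are also worded differently. Non-completion refers to the maximal modules and completion simply to modules, while the section on tailored IMIs says that some trainings offer additional modules. Whether maximal includes these is not stated.

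**2. Overlap from the inactivity item, if the bracket items are alternatives**

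Assumed inputs: N = 100 starters, the number the protocol calls desirable per intervention, used here only as a scale; p = share reaching the threshold; q = share of those with an 8-week gap or an interruption. Neither p nor q is in the document.

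- Completed = N × p
- Not completed = N × (1 − p) + N × p × q
- Double count = N × p × q

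| p | q | Completed | Not completed | Sum |
|---|---|---|---|---|
| 0.5 | 0.1 | 50 | 50 + 5 = 55 | 105 |
| 0.5 | 0.3 | 50 | 50 + 15 = 65 | 115 |
| 0.5 | 0.5 | 50 | 50 + 25 = 75 | 125 |
| 0.7 | 0.1 | 70 | 30 + 7 = 37 | 107 |
| 0.7 | 0.3 | 70 | 30 + 21 = 51 | 121 |
| 0.7 | 0.5 | 70 | 30 + 35 = 65 | 135 |

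If non-completion took precedence at p = 0.7, completers would be 70 − 7 = 63, 70 − 21 = 49 or 70 − 35 = 35. If the stem limits all items, this double count is zero and the sum is 100. Each late passer from step 1 would then still add one.

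**3. Tele denominator**

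Fraction completed = minutes delivered ÷ total minutes T. As an example dose, take the minimal telephone treatment that the Reach section itself cites: 6 × 15 = 90 minutes at most.

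- At least 50% requires T ≤ 90 ÷ 0.5 = 180 minutes.
- At least 70% requires T ≤ 90 ÷ 0.7 = 128.6 minutes.
- Assumed T = 120: 75%, completer on both criteria.
- Assumed T = 150: 60%, completer at 50% only.
- Assumed T = 300: 30%, completer on neither.
- T = the person's own delivered minutes: 100% for everyone.

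**The case against.** The strongest reply rests on the stem. It defines non-completers as people below the threshold, and the bracket can be read as describing how such people stop being in treatment. Table 1 and the section Measuring implementation success also treat the two labels as opposites. This reading is fair. A reader might infer that 8 weeks without a login turns anyone, even a full completer, into a non-completer. The document does not establish that; it is one of two readings. The dose condition is repeated only in the first bracket item, which leaves the other reading open, and no precedence rule settles it. The reply does not remove the one-sided 13-week limit.

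On tele, Fig. 3 covers the usual duration of coaching, and the supplement holds an intervention description. Neither is shown. The Maintenance section speaks of prolonging a coaching, which suggests a base amount. So one cannot say that no reference amount exists, only that the text shown does not identify it as the denominator.

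There are also partial safeguards. The coach rating supplements the dose criteria, although nothing says it reclassifies anyone. The number and duration of contacts are already monitored. Implementation success is evaluated separately by intervention, although the regression of uptake on intervention type remains. Reporting both 50% and 70% is deliberate, and a person who changes class between the two thresholds is not an error.

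**Conclusion.** The point holds as a defect of definition, of moderate severity. The 13-week limit on one side only lets the same IMI participant meet both rules. The inactivity and interruption items may add further overlap, depending on how the bracket is read. Tele-coaching has no window, and its denominator is undefined in the text shown.

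The size cannot be computed from the document. The sums of 105 to 135 per 100 starters hold only under the alternatives reading and the assumed p and q; under the stem reading, the inactivity item contributes nothing. A reader might go further and conclude that the completion figures will be wrong, or that the two services cannot be compared. The document supports only that the figures are ambiguous and that the comparison is at risk. Completion is an uptake level and an indirect acceptance measure here, and no passage makes it a primary hypothesis test.

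**What to change.** At each threshold, classify every starter once, at one fixed time per service counted from a named start:

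- **Completed:** threshold reached by that time.
- **Not completed:** below the threshold and inactive for at least 8 weeks, stopped, or window elapsed.
- **Still in treatment:** below the threshold, active, window open. Keep this apart from the existing in-treatment level, which counts everyone who started.

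Apply the inactivity and interruption rules only below the threshold. Use the same module denominator in both IMI definitions. For tele, name one reference amount fixed in advance, not the minutes delivered and with prolongation not added; if Fig. 3 gives such an amount, refer to it. Report the number and duration of contacts, already monitored, next to the tele-versus-IMI uptake comparison.

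The start must be named because the Effectiveness section counts its post-treatment assessment from first platform login or registration, whereas the Reach section dates the start of treatment from the first module or the second coaching session.

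The cost is mainly wording, settled before participants are classified. Late completers will count as non-completers, and the tele provider may need one field for the planned amount.
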